### Outcome Measures

Outcome domains were selected based on the intervention’s theoretical framework and logic model (Figure S1 in Multimedia Appendix 1) and included primary outcomes of QOL, along with secondary and measures capturing psychosocial, behavioral, cognitive, and biological responses.

### Primary Outcome

The primary outcome of this study was participants’ QOL using the WHOQOL-BREF (World Health Organization Quality of Life−brief version), a multidimensional QOL tool developed by the World Health Organization. The instrument consists of 25 questions evaluating 4 domains of QOL, namely physical (7 items), psychological (6 items), social relationships (2 items), and environment (8 items). One item in the social dimension—“How satisfied are you with your sex life?”—was removed because it was considered culturally sensitive for this study population. The items that were negatively worded had their scores inversed. In addition, there were also 2 questions about general QOL and health satisfaction questions. The physical health domain measures individuals’ biological well-being related to the body and its functions. The psychological domain examines the aspects of mental well-being and cognitive functioning. Social relationships were based on interpersonal connections and support systems. The environment domain covers factors related to surroundings and external conditions [32]. Higher scores in each of the 4 domains indicate better QOL. The score of the 4 domains was summed together, where a higher score indicated a higher QOL. The validity and reliability of the WHOQOL-BREF were tested in Singapore in Chinese, English, and Malay. The instrument is valid and reliable for assessing the QOL among English-, Chinese-, and Malay-speaking people in Singapore [33].

### Secondary Outcomes

#### Physiological Outcomes

The physiological component included changes in cardiometabolic outcomes. The cardiometabolic outcomes consisted of the following physical measurements: (1) waist circumference and hip circumference, (2) systolic and diastolic blood pressure, (3) resting heart rate, (4) body weight, and (5) height and BMI. Weight and height were measured without shoes. BMI was calculated by dividing weight in kilograms by the square of height in meters. Systolic and diastolic blood pressures were measured after the participants had rested for at least 5 minutes [34]. Waist circumference (cm) was measured at the middle point between the lowest rib in the standing position and the iliac crest.

#### Frailty

Participants’ frailty was assessed using the Fried frailty phenotype [35], which consists of 5 components: unintentional weight loss, exhaustion, weakness, slowness, and low physical activity. Each of the components was calculated using the computation methods described in [35, 36]. Weight loss was a self-reported item to determine if participants had lost 4.5 kg or more in the past year. Exhaustion was assessed through 2 self-reported feelings of fatigue and low energy. Physical activity was evaluated based on self-reported items on walking for 30 minutes or more a day and the amount of time spent sitting. Weakness was measured using grip strength, with scores computed according to gender and BMI-specific cut-offs, where values below the threshold indicated weakness. Slowness was assessed using a 5-m walking speed test, with thresholds for slowness determined according to gender and height; scores above the threshold indicated slowness. Frailty scores were computed and categorized into non-frail (none or 1 criterion met), pre-frail (2 criteria met), and frail (3 or more criteria met) [35, 36].

#### Biomarkers

Fasting blood was collected and sent to a certified laboratory. Around 10 mL of blood was collected in each data collection. In addition, clinical bioprofiling, such as the assessment of plasma glucose, hemoglobin A_1c_, and lipid panels (total cholesterol, triglyceride, low-density lipoprotein cholesterol, and high-density lipoprotein cholesterol), and serum creatinine were examined. Plasma biomarkers were analyzed using commercially available enzyme-linked immunosorbent assay and bead-based multiplexing Luminex system immunoassay kits. Evaluated analytes involved several functions: inflammation, immune system adaptation, senescence, and cellular signaling. More specifically, the targeted biomarkers assessed cytokines involved in innate immune functions (interleukin-1 receptor antagonist, interleukin-1 beta, interleukin-6, interferon-gamma-induced protein 10, tumor necrosis factor alpha), adaptive immunity (interferon gamma, interleukin-10, interleukin-13, interleukin-17A), macrophage inflammatory markers involved in aging altering cellular communication and inflammatory state (macrophage inflammatory protein-3 beta, stromal cell-derived factor-1 alpha, matrix metalloproteinase-3, matrix metalloproteinase-9, monocyte chemoattractant protein-1, plasminogen activator inhibitor-1, granulocyte-macrophage colony-stimulating factor, vascular endothelial growth factor A), and chemokines (eotaxin, interleukin-8). Study participants with abnormal biomarkers were encouraged to consult with a physician.

#### Psychosocial Outcomes

A range of psychosocial measures was adopted. To measure social well-being, the Lubben social network scale [37] was used. The De Jong Gierveld Loneliness Scale [38], which has 6 items, was used to measure social and emotional loneliness. The Brief Sense of Community 8-item scale was employed to assess participants’ perceptions of utilizing community resources to fulfill their needs [39]. Older adults’ resilience was measured using the Brief Resilience Scale [40]. The 10-item Perceived Stress Scale was adopted to measure psychological stress [41].

#### Cognitive Outcomes

The Montreal Cognitive Assessment (MoCA) was adopted to evaluate cognitive function, with assessment categorized into memory, executive functioning, attention, language, visuospatial skills, and orientation domains [42]. The maximum total score was 30, with a cutoff of 26 or above indicating a normal cognitive function. Additionally, functional near-infrared spectroscopy (fNIRS) was collected. fNIRS measures hemodynamic changes in the cerebral cortex over time, reflecting neuronal activity via neurovascular coupling. Near-infrared light penetrates tissues to the cortex, where it is absorbed by oxyhemoglobin and deoxy-hemoglobin. Increased neuronal activity will lead to a net rise in oxy-hemoglobin and a slight decrease in deoxy-hemoglobin, making oxy-hemoglobin a marker of cortical activity. Participants were asked to perform a semantic verbal fluency task during each fNIRS measurement. The verbal fluency task consisted of alternating blocks of 4 control periods and 3 task periods. Each control and task period was 30 seconds long. Participants were instructed to say the names of the weekdays consecutively and generate words that belong to a particular category (eg, fruits, flowers, professions) during task periods [43]. Categories differed between task periods and fNIRS measurements. The total number of words generated per category was noted.

#### Dietary Outcomes

Participants’ attitude and behavior toward healthier diet consumption, for example, consumption of fruits and vegetables, were measured. Participants’ healthy eating behavior was also assessed by indicating the frequency of consuming food from various groups (eg, vegetables, fruits, fried snacks, sweet snacks, fast food, sweet drinks, fruit juice) and their willingness to consume fruits and vegetables. Attitude toward healthy eating was measured by an 11-item scale [44].

#### General Life Satisfaction

A single-item measure, “In general, how satisfied are you with your life as a whole?”, was adopted. Participants ranked a 10-point scale, with 1 being “very unsatisfied” and 10 being “very satisfied.” The single-item satisfaction with life measure is a validated instrument that performs similarly to the multiple-item satisfaction with life scale [45].

### Exploratory Outcomes

Physical activity was measured with Fitbits. The intervention group was given a Fitbit Inspire 2 or Inspire 3 device to track their step count throughout the trial. Fitbit is an activity device that uses a tri-axis accelerometer to provide real-time feedback and allows self-monitoring of steps. Participants were encouraged to wear the device as frequently as possible to obtain the most accurate results. Fitbit intraday data were downloaded, providing minute-by-minute data that was available through a web application programming interface.

### Sample Size

This study aimed to compare the QOL between the treatment and waitlist control participants, using a 1:1 allocation ratio. Based on a prior study of the overall WHOQOL measure, if the true difference-in-differences estimate between experimental and control means is 4.93 with a standard deviation of 9.29 [46], a sample of 57 intervention and 57 control subjects is required to reject the null hypothesis based on a 2-tailed significance level of 5% and power of 80%. We inflated the sample by 20% to account for dropouts and the potential loss of participants due to noncompliance and faulty measurements. Accounting for all these factors, the total sample size required for 2 arms is 138 participants.

### Recruitment

Singapore residents were invited to participate in this study. We adopted a 2-prong recruitment strategy. First, we collaborated with local community partners and senior activity centers (SACs) to recruit potential participants. The findings from our feasibility study suggest that older adults are more inclined to participate when approached through familiar and trusted sources. Concurrently, we simultaneously conducted open recruitment by promoting the study via social media and word of mouth. Although this second approach engaged young-old adults, some have encouraged their parents to join the study. Our recruitment approaches ensured effective outreach to our target audience of older adults. Recruitment occurred between February and March 2024. During the recruitment phase, the research team was in close contact with SACs and community partners to facilitate recruitment. During recruitment, interested participants, recruited from either partnered SACs or online recruitment, provided their contact details on a sign-up form. Subsequently, a research staff member contacted these participants to share more information about the study and screened them first for their age eligibility. Those who met the criteria were invited to a briefing session where more detailed information about the research was presented. Informed consent was obtained from participants who agreed to participate and were enrolled in this research study. Participation was voluntary, and participants could withdraw from the study at any time without reason or penalty.

### Blinding and Assignment of Groups

Participants were randomized into either of the groups based on a computer-generated random generator using Stata 14 [47]. A first block of 130 participant IDs was randomly generated, followed by a second block of 20 due to additional recruitment. At baseline data collection, all participants and data collectors were blinded to group allocation. Randomization and allocation results were shared only at the last station after written informed consent and the completion of all baseline data to ensure allocation concealment. To maintain neutrality, the research staff who generated the randomization were independent of the staff responsible for revealing group allocations to participants. As the nature of the intervention required participants to be involved in the study, both participants and research staff were eventually aware of group allocation. All outcome assessments were conducted by trained assessors who were independent of intervention delivery. Assessors were blinded to participant group allocation at baseline and 6-month and 12-month follow-up, where feasible. However, full blinding could not always be maintained during follow-up, particularly when participants disclosed their participation during data collection. To mitigate potential bias, the assessors were trained to ensure accurate and objective data collection, and validated instruments were used to reduce subjectivity in cognitive and psychosocial outcomes.

### Data Collection and Analysis

#### Data Collection

Baseline data were collected after informed consent was obtained. Table 2 outlines the measures and instruments that were collected in each of the 3 assessment time points. At baseline (T0) and 6-month follow-up (T1), participants completed the survey, blood test, fNIRS, MoCA, and physiological assessments at the National University of Singapore. At the 12-month follow-up (T2), all the assessments completed at T0 and T1 were repeated, except for the blood test and fNIRS. Participants were invited to return to the same location for T2 data collection. However, we anticipated that some participants may be unwilling or unable to return in person. For those who did not attend the in-person assessment, a survey link was sent to them to allow them to self-administer remotely. The rest of the assessment was not collected from these participants. To maximize the data collected, participants were reimbursed a small amount of S$30 (US $22.05) [30] each for T0 and T1 assessments, and S$20 (US $14.70) [30] for T2 in-person assessment or S$10 (US $7.35) [30] for completing the T2 online self-administered survey. The physiological assessments were collected by trained research assistants, while blood samples were collected by certified phlebotomists or registered nurses. The survey was available in English and Chinese and was self-administered by participants; however, trained research assistants assisted participants who were illiterate in either of the languages to complete the survey. fNIRS data were collected by a trained engineer.

**Table 2. T2:** Overview of study outcomes and measurement instruments used.

	Feasibility	Baseline	6-month	12-month
Demographics				
Age	✓	✓	✓	
Gender	✓	✓	✓	
Ethnicity	✓	✓	✓	
Marital status	✓	✓	✓	
Education	✓	✓	✓	
Pre-existing diseases, self-reported		✓	✓	✓
Smoking and alcohol consumption	✓	✓	✓	
Community participation	✓	✓	✓	
Quality of life: WHOQOL-BREF^a^		✓	✓	✓
EQ-5D-5L	✓	✓	✓	✓
Psychosocial				
Lubben social network scale	✓	✓	✓	✓
De Jong Gierveld loneliness scale	✓	✓	✓	✓
Brief sense of community		✓	✓	✓
Brief resilience scale	✓	✓	✓	✓
Perceived stress scale	✓	✓	✓	✓
Satisfaction with life	✓	✓	✓	✓
Physical activity				
Fitbit tracking	✓	✓	✓	
Dietary				
Attitude toward consumption of fruits and vegetables	✓	✓	✓	✓
Fruits and vegetable consumption frequency (behavior)	✓	✓	✓	✓
Cognition				
Functional near-infrared spectroscopy		✓	✓	
Montreal cognitive assessment	✓	✓	✓	✓
Physiological outcomes				
Body weight and height	✓	✓	✓	✓
Waist and hip circumference	✓	✓	✓	✓
Blood pressure	✓	✓	✓	✓
Resting heart rate	✓	✓	✓	✓
Fried phenotype of frailty		✓	✓	✓
Biomarkers				
Fasting plasma glucose, HbA_1c_^b^		✓	✓	
Fasting insulin		✓	✓	
Lipid profile: triglyceride, total cholesterol, high-density lipoprotein cholesterol, low-density lipoprotein cholesterol		✓	✓	
Cytokines: interleukin-1 receptor antagonist, interleukin-1 beta, interleukin-6, interferon-gamma-induced protein 10, tumor necrosis factor alpha		✓	✓	
Chemokines: eotaxin, interleukin-8		✓	✓	
Adaptive immunity: interferon gamma, interleukin-10, interleukin-13, interleukin-17A		✓	✓	
Macrophage inflammatory markers: macrophage inflammatory protein-3 beta, stromal cell-derived factor-1 alpha, matrix metalloproteinase-3, matrix metalloproteinase-9, monocyte chemoattractant protein-1, plasminogen activator inhibitor-1, granulocyte-macrophage colony-stimulating factor, vascular endothelial growth factor A		✓	✓	

a WHOQOL-BREF: World Health Organization Quality of Life−brief version.

b HbA_1c_: hemoglobin A_1c_.

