**Methods:**

We conducted a parallel group, 2-arm pragmatic waitlist randomized trial with a 1:1 allocation, in which participants were randomized into either the intervention or waitlist control arm. Community-dwelling participants aged 50-85 years, without any mobility issues, were recruited. Participants in the intervention arm commenced the 24-week UCF program, while waitlist control participants received no intervention during this period. The primary (World Health Organization Quality of Life−brief version) and secondary outcomes were collected at baseline, 6th month, and 12th month after the intervention group completed the trial. Secondary outcomes include objectively measured physiological outcomes, cognition, frailty, and self-reported psychosocial outcomes. Intervention effects were estimated using mixed-effects difference-in-differences regression to account for repeated measurements.

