#### Statistical Analysis

The primary analysis, intention-to-treat, will be conducted using a linear mixed effects model with overall WHOQOL score as the dependent variable and the interaction effect of intervention allocation and time as the independent variable. Domain-specific scores will also be analyzed. To address potential bias arising from missing data due to attrition or incomplete responses, our primary longitudinal analyses will employ linear mixed-effects models, which are robust to unbalanced data structures and can handle missing observations under the missing-at-random assumption. While listwise deletion may be used for cross-sectional comparisons or descriptive analyses, this will be clearly indicated. Secondary outcomes will be analyzed using similar methods. These analyses will be conducted at 6-month follow-up to investigate the effectiveness of the intervention as well as post-intervention behavioral maintenance at 12 months. Sensitivity analysis using the per-protocol approach will also be carried out. Baseline characteristics of participants who discontinued or were lost to follow-up will be compared to those who completed the study to investigate differential dropout between intervention and control groups.

Due to potential imbalances between the groups, further analysis techniques, such as adjustment or matching of baseline characteristics, will be used in the difference-in-difference analysis. Specifically, we will adjust or match on key baseline covariates (eg, age, gender, years of education, marital status, and housing type) to improve group comparability at baseline in case of any imbalance despite randomization. This approach improves covariate balance and enhances the comparability of groups prior to applying linear mixed models for outcome analyses. Conducting both intention-to-treat and per-protocol analyses for this behavioral intervention allowed comparison of the results and provided a comprehensive understanding of the treatment effect. All evaluations were and will be performed using a 2-sided test at the 5% level of significance.

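### The 12-month secondary analysis is stated without exception, but blood markers and fNIRS were not measured then, and in-person measures exist only for those who attended

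*Protocol article*

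**What the plan says.** The abstract's Methods paragraph says that "secondary outcomes were collected at baseline, 6th month, and 12th month after the intervention group completed the trial". Under Statistical Analysis, "Secondary outcomes will be analyzed using similar methods", and these analyses are to run at 6 months for effectiveness "as well as post-intervention behavioral maintenance at 12 months". Neither place excepts any outcome.

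Data Collection says of the 12-month visit (T2) that "all the assessments completed at T0 and T1 were repeated, except for the blood test and fNIRS". Table 2 agrees: fNIRS and every biomarker row lack a 12-month tick, while MoCA, the Fried phenotype, weight and height, waist and hip, blood pressure and heart rate have one. Biomarkers and fNIRS are both listed under Secondary Outcomes.

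The same section expected that "some participants may be unwilling or unable to return in person". Those people were sent the survey link, and "The rest of the assessment was not collected from these participants". Table 2 schedules WHOQOL-BREF and EQ-5D-5L at 12 months.

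For missing data, Statistical Analysis relies on linear mixed models that "can handle missing observations under the missing-at-random assumption". It also plans a baseline comparison of completers with participants who discontinued or were lost.

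**The concern.** There are two separate problems.

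First, the reach of the 12-month analysis does not match the schedule. A reader of the abstract would expect 12-month biomarker and fNIRS evidence, and none can exist.

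Second, the measures that need a visit are observed at T2 in a self-selected group. For frailty, physical function and cognition, the reason for staying away may be linked to the quantity being measured. A mixed model fitted to one outcome corrects for absence that the earlier values of that outcome explain. It does not correct for a change in health after 6 months. The trial holds information on exactly that, in the 12-month survey answers of the remote responders, and the stated model leaves it out.

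The planned dropout comparison does not clearly cover these people either. The Figure 1 legend defines dropout as withdrawal or loss of contact, and a remote responder is neither. At stake is whether a finding of sustained frailty, cognition or physiological status at 12 months reflects the whole arm or only those who came back.

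**Working it through.** **Schedule against analysis statement**

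| Outcome group | T2 data by design | Consequence at 12 months |
|---|---|---|
| Blood markers, fNIRS | none (0 of 137) | no estimate possible |
| MoCA, grip, 5-m walk, anthropometry, blood pressure, heart rate | in-person attenders | estimable under missing at random |
| Psychosocial, dietary, life satisfaction, WHOQOL-BREF | attenders and remote responders | not affected by this gap |

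Three of the five Fried components (weight loss, exhaustion, physical activity) are self-reported. Weakness and slowness need a visit, so the full Fried count does too.

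**Size of a possible bias within one arm**

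The article gives no figure for this, so there is nothing of its own to reproduce. All inputs below are assumptions: outcomes in SD units; correlation 0.7 between successive visits, with Y2 = 0.7·Y1 + √(1 − 0.49)·e, and Y1 built from Y0 in the same way; a T2 survey score A correlated r with Y2; and logit P(remote) = c − 1·D, where D is the driver of absence and c is set to give 20% or 30% remote. Bias is the estimated minus the true T2 mean, from large simulated samples. The history-only column regresses Y2 on Y0 and Y1 among attenders and averages the predictions over everyone, which stands in for the mixed model. The last column adds A.

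| Driver of absence | r | Attenders only (20% / 30%) | History only | History plus survey score |
|---|---|---|---|---|
| Current outcome Y2 | 0.7 | 0.17 / 0.25 | 0.09 / 0.14 | 0.06 / 0.10 |
| Current outcome Y2 | 0.3 | 0.17 / 0.25 | 0.09 / 0.14 | 0.09 / 0.13 |
| Survey score A | 0.7 | 0.12 / 0.18 | 0.06 / 0.09 | 0.00 / 0.00 |
| Earlier value Y1 | 0.7 | 0.12 / 0.18 | 0.00 / 0.00 | 0.00 / 0.00 |

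With 10% remote, the history-only bias is 0.05 SD (driver Y2) or 0.03 SD (driver A). With the slope halved to 0.5 and driver Y2, it is 0.05 / 0.08 SD at 20% / 30% remote.

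**Between-arm contrast**

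Assume no true difference, attendance correlated 0.3 with a better change, and complete-case means.

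| In-person share, intervention / control | Bias in intervention-arm change | Between-arm bias |
|---|---|---|
| 80% / 80% | +0.10 SD | about 0 |
| 60% / 80% | +0.20 SD | +0.09 SD |
| 80% / 60% | +0.10 SD | −0.09 SD |

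The sign turns on which arm attends less.

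**The case against.** The case against has six parts.

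- **Disclosure.** Data Collection and Table 2 openly show that blood and fNIRS were dropped at T2, and the maintenance phrase can be read as covering behavioral outcomes alone. This softens the conflict in Statistical Analysis. It does not remove it, because that sentence follows directly on all secondary outcomes, and the abstract has no such qualifier.
- **Scope.** A reader might infer that no 12-month secondary analysis can be derived. That holds only for blood and fNIRS. Survey outcomes were offered to everyone, and the visit measures can be estimated from attenders under the stated assumption.
- **Who stayed away.** A reader might infer that the missing participants are those unable to travel. The text says unwilling or unable. Entrants were ambulant, a session took about 210 minutes, and in-person payment fell from S$30 to S$20 at T2, so reluctance unrelated to health is plausible.
- **Direction.** A reader might infer that the gap necessarily flatters maintenance. For the planned allocation-by-time contrast the sign is undetermined. Within the intervention arm, flattery is possible if healthier people attend. That reading matters here because controls had received the program by 12 months, so maintenance is largely a within-arm question. It remains an assumption.
- **Value of imputation.** If absence follows the current outcome and the survey score correlates only 0.3 with it, almost nothing is gained. Nothing in the article supports 0.7 for MoCA, blood pressure or weight. Imputation should therefore stand beside the mixed model and not replace it.
- **Deferral to an analysis plan.** Auxiliary variables and sensitivity analyses are commonly specified there. This limits the criticism to what the article itself fixes: the unrestricted 12-month statements and the named missing-data remedy.

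**Conclusion.** The point holds in a limited form. Blood markers and fNIRS have no 12-month data, and the abstract and Statistical Analysis section must be reconciled with Data Collection and Table 2. This part needs no assumption.

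For the visit-based measures, the stated mixed model is adequate if attendance depends on earlier values of the same outcome. If it depends on current health, the 12-month mean within an arm may be off by about 0.06 to 0.14 SD. That range assumes 20% to 30% remote, visit-to-visit correlation 0.7 and a log-odds slope of 1 per SD. It shrinks with a smaller remote share or a weaker slope, and is about 0 if absence follows 6-month values. The article gives neither the remote share nor the reasons for it, so no actual bias is shown, and the direction of any between-arm bias is open.

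Using the 12-month survey scores never increased the bias in these scenarios, and removed it when absence followed the survey score. The primary outcome is collected in the survey and is not affected by the loss of in-person measures.

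**What to change.** 1. For outcomes that needed a visit at T2, keep the mixed model and add an analysis by multiple imputation within arm. Use the baseline and 6-month values plus the T2 survey scores: EQ-5D-5L, the WHOQOL-BREF physical domain, and the self-reported Fried items where the survey carries them. Report the numbers and characteristics of in-person and remote participants by arm. State that this reduces but does not remove bias if absence depends on the unmeasured outcome itself.
2. Restrict the 12-month statements in the abstract and in Statistical Analysis to outcomes measured at T2, and name blood markers and fNIRS as 6-month only.

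The cost is wording and analysis time, with no new data collection. The downside is an imputation model to specify, and possibly slightly wider 12-month intervals.
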